### Testing strategy

The question of “who to test” and “how to test” in LMICs was discussed in a recent article (12). WHO recommended « that HCV serology testing be offered to individuals who are part of a population with high HCV seroprevalence or who have a history of HCV risk exposure/ behavior » (13). This recommendation includes « persons who have received medical or dental interventions in health-care settings where infection control practices are substandard » which was the case of Cambodia before years 2000. Targeted HCV testing interventions to individuals who are a part of risk groups for HCV infection or who have a history of HCV risk behaviors seems to be effective to diagnose cases and increase treatment uptake (14) but the reported programs are mainly heterogenic, and the majority did not use a comparison group (15). However, many countries in Europe and US recommend a systematic population-based screening for groups at risk of infection. In US, excepting classic at-risk groups (injecting drug use, hemodialysis, and prisoners), HCV infection is most prevalent among individuals born between 1945 and 1965 (baby-boomer population) (U.S. Department Of Health And Human Services/Centers for Disease Control and Prevention (CDC). HEPATITIS C: Why Baby Boomers Should Get Tested). Since 2012, CDC recommends HCV screening in this population. In France, recommendation changed in 2014: HCV screening must be done for all men aged 18-60, with also a particular warning for the baby-boomer population, as many persons are still undiagnosed in 2014 in this population(16). Screening could be done in different medical structures (17)(18)(19)(20) and could easily be integrated in routine primary care (21).

Nevertheless, all these studies were conducted in high-income countries and data in low-income countries are scarce. Rapid diagnosis tests are available in the majority of these countries but targeted testing interventions are related to country’s epidemic situation and to the health care structures. Community approach with testing at a household level was reported effective in Egypt

to ensure both high uptake of testing, and equity in access regardless of sex, age, income level, or stage of disease (22). As recommended by WHO, « Operational research is needed to evaluate different approaches to increase the reach and uptake of screening services ».

However, a comprehensive and integrated approach to the elimination of HCV at a community level, must incorporate both preventive approaches to reduce transmission and new infections, and testing and treatment to reduce both the burden of disease and associated morbidity. A prompt linkage to care to ensure access to treatment is essential. In the Egyptian publication, the treatment coverage and cure were over 90% of the estimated HCV-infected village population.

### HCV RNA quantification

WHO suggest that nucleic acid testing for the detection of HCV RNA be performed directly following a positive HCV serological test to establish the diagnosis of chronic HCV infection and that all patients with positive HCV RNA should be assessed for the treatment.

HCV RNA availability in resource-limited setting is challenging. HCV RNA could be done on plasma but requires syringes, tubes, centrifuges machines and skilled human resources. The Cepheid Xpert HCV viral load assay could be an alternative to central laboratory equipped for classical virological diagnosis (23)(24). The limited operator input allows considering an implementation in provincial hospital and a recent article report a good accuracy on finger-stick capillary whole blood (25). However, patient needs to come to provincial hospital, which could increase the risk of lost-to-follow-up after a positive Ab. And the total number of possible samples evaluated each day is limited, which could be challenging for a scale-up strategy.

The performance of the Omunis Generic HCV assay on an open polyvalent PCR platform was recently evaluated in France and Cambodia (26); this HCV PCR assay showed good concordances in clinical specimens when compared to the Roche assay. The cost per test of the Generic HCV assay has been estimated by MSF Access Campaign at \$22.6 including the Arrow automated extraction kit and proteinase K reagent, which is close to the cost per test of the Cepheid Xpert HCV viral load assay estimated at \$18 (27). This affordable HCV test could represent a surrogate method to manufacturer's PCR systems for the diagnosis and monitoring of HCV RNA testing in central laboratories from low- and middle- income countries. It could allow 40 to 82 samples per day and could be used on plasma or DBS (27). DBS could represent an alternative to simplify and decentralize access to HCV RNA, specifically at community level. DBS could easily be sent to equipped central laboratory and HCV RNA performed at this level. The performance seems good but sensitivity seems altered for patients with low-level viremia (28) and HCV RNA degradation could occurred in DBS samples stored at room temperature (29).

### Linkage to care and access to treatment

Specific HCV services with nurse educational interventions and access to treatment increase retention in care, treatment completion and cure (30). Considering the high chance of cure for HCV infection after DAA treatment, reaching elimination target seems to be a non-utopian option if interventions to improve the cascade of care are implemented (31) and some countries, as Georgia, have implemented national programs to eliminate HCV infection with access to DAA whatever the fibrosis assessment (11).

Many DAA combinations has proved to be effective in Asia (32) but cost and affordability remains the major issue. In Cambodia, genotypes 1 and 6 represent almost 95% of HCV infections and genotype 2 is reported in 5% of cases (6)(7). Association of sofosbuvir and daclatasvir was reported to be effective for these 2 genotypes (33)(34) but also recently for genotype 3 (35) and is affordable at low price in the country. In a public health approach, it could be cost-effective to treat all the patients as it was recently reported in Korea (36).

### **Health care system organization in Cambodia**

Private practitioners and clinics are particularly frequented for curative care, whereas health promotion and prevention activities are the domain of the public sector. The low utilization of the public health facilities for curative care remains a concern. Only 29% of unwell or injured patients sought care first in the public sector, while 57% sought care for their last episode at private providers, according to the 2010 Cambodian Demographic and Health Survey.

Public health services are available through a national network of Health Centers and Referral Hospitals; in principle, primary care services are available within two hours walk from home for the whole population:

- Health Centers provide maternal, neonatal and child health services, including immunization, nutritional education, screening for breast and cervical cancer, safe abortion; treatment and prevention of communicable diseases; treatment and prevention of NCDs (Non Communicable Diseases) and injuries; and through outreach activities.
- District Referral Hospitals provide outpatient care as well as inpatient treatment for referred cases, complicated tuberculosis cases, medical, surgical and obstetrical emergency cases, some surgery, maternal and child health services, provision of X-ray, ultrasound and laboratory services, and rehabilitation services.

However, many patients go straight to hospitals, bypassing the health centers.

Provincial Health Departments (PHD) operate a provincial hospital and cover from one to 10 Operational Districts (OD). Each OD covers a population of 100 000–200 000 with at least one Referral Hospital (RH) and a number of Health Centers (HC) that each cover 10 000–20 000 people.

As part of health system development, in 2003 (revised in 2008), the Community Participation Policy for Health was created and implemented, highlighting a key role for community health workers (CHWs) (37). Programs implementation are financed and supported by Provincial Health Departments (PHD) and the administrative Operational District (OD) in terms of structure and management. Each CHW is associated with a health centre where they could receive training and supervision and in some cases resources to support their role. The policy states that CHWs should be literate, live in the communities they serve and be elected by community members. Each CHW serves between 10 and 50 households depending on the community need. The CHWs are not a homogeneous group and vary widely in age, gender, experience, social status and political affiliation. Their roles include responsibility to analyze and identify health issues arising in the community and communicate these to health centres and to share information from health centres with the community. However, they face many challenges as lack of financial support, lack of training and lack of community interest and participation (38).

### **Study main hypothesis**

- Comparative testing interventions is a prerequisite to improve the cascade of care
- Population aged more than 40 years old must be targeted in priority
- Testing interventions must include serological and virological tools as a package to improve active case detection
- Community approach using RDT/DBS combination could increase the testing uptake and the active case detection compared to facility approach
- The relevance of a systematic treatment is fully realized for all patients with active infection, most at risk of severe fibrosis and liver cancer. This strategy will not be compared and implemented in the 2 arms.

## 4. OBJECTIVES OF THE STUDY

### Primary objective

The primary objective of the study is to compare the effectiveness of a community-based intervention to a facility-based intervention to improve the combined-testing uptake (Antibody + RNA) of HCV infection among general population aged more than 40 years old in Cambodia

### Secondary objectives

- To compare the HCV antibody testing uptake between the 2 arms for the eligible population
- To compare the active case detection rate between the 2 arms for the eligible population
- To compare the linkage to care between the 2 arms for those with active infection
- To compare the cost-effectiveness of the two strategies
- To evaluate the treatment uptake
- To evaluate the effectiveness and safety of a 12-week dual-therapy of direct-acting antiviral (DAA) treatment

## 5. METHODOLOGY

### Study design

This is a two-arms cluster-randomized controlled trial, in which clusters are defined as a group of 50 households corresponding to the service population of the CHWs.

The study will be conducted in 2 different provinces.

### Study overview

A facility-based testing intervention (group 1) will be compared to a community-based intervention (group 2). The study will be conducted in 2 separated provinces: Siem Reap and Kampong Cham provinces. Each province has approximatively one million of inhabitants and one

provincial hospital. Siem Reap province is composed of 4 ODs, 103 communes, 5 RHs and 88 HCs. Kampong Cham province is composed of 9 ODs, 107 communes, 9 RHs and 98 HCs.

For the study, one OD in Siem Reap province and 2 ODs in Kompong Cham province with approximately the same number of villages and inhabitants and the same distance from PHD will be selected. The districts are sub-divided into communes. Communes are further divided into villages. Villages are sub-divided into groups. A group is generally a combination of 50 households and one group will be defined as one cluster.

In order to decrease the risk of contamination between clusters, in each province, 4 geographic area, separated by communes not involved in the study, will be selected. A random selection of the geographic area in each province will be done to be part of arm 1 or 2.

**For each geographic area**, a multistage cluster sampling method will be used to select study participants:

1- A Probability proportional to size (PPS) sampling method to select 10 villages in each selected GA will be realized in a first step

2- Then, a preliminary mission will be organized in order to identify and confirm the location of HHs in the 10 selected villages. During this mission, information on age of inhabitants will be collected with the heads of village and a list of HHs will be identified

3- A Simple random sampling (SRS) method will be realized to select 100 households per village within the 10 selected villages

4- In each selected household, all persons aged more than 40 years old will be proposed to be part of the study.

### **Tentative study agenda**

First inclusion: May 2022

Inclusion time: 6 months.

Time of follow-up for each participant: 6 months

Last visit for the last patient: April 2023

## **6. STUDY POPULATION**

### **Inclusion criteria**

- All persons aged more than 40 years old
- Residing in the study area
- Informed consent obtained with oral information given and explained and the consent form signed by the participant and the nurse hired by the study at the latest the time of the RDT realization

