## 7. STUDY ENDPOINTS

### Primary endpoint

The primary endpoint is the **combined-testing uptake** defined as the number of persons tested for HCV RDT AND HCV RNA and aware of their status among the total number of persons eligible residing in the region where the intervention takes place

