### Secondary endpoints

The following secondary endpoints will be measured and compared between the 2 arms:

- **HCV antibody testing uptake** defined as the number of persons tested for HCV RDT and aware of their status among the total number of persons eligible residing in the region where the intervention takes place
- **Active case detection rate** defined as the number of persons with HCV active infection (positive HCV Ab and positive HCV RNA) and results given and explained among the total number of persons eligible residing in the region where the intervention takes place
- **Linkage to care** defined as the number of persons with at least one consultation in the Provincial Hospital among the estimated total number of persons with active infection residing in the region where the intervention takes place

The following secondary endpoints will be measured for the total population and not compared:

- **Treatment uptake** defined as the number of people initiating HCV treatment among the total number of persons with active infection linked to care
- **Liver-related morbidity and mortality** (decompensated cirrhosis, HCC)
- Proportion of patients with sustained virologic response 12 weeks after discontinuation of treatment (**SVR12**)
- Proportion of patients with **treatment failure** defined as absence of SVR12 or missing HCV-RNA at 12 weeks post-treatment (PT12) due to treatment discontinuation for AEs or death

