### Arm 2: Community-based testing intervention

After a dedicated training, CHWs will do the HCV RDT on a finger stick capillary whole blood directly in the household of participant. Information will be provided by the CHW using information sheet and a dedicated leaflet. If the participant agrees to participate, the signed consent form will be collected at this step before any RDT collection. In case of structural or societal barriers for household testing, it will be possible to provide testing in a specific location in the village. The visits will be planned with the head of village and he will be in charge to inform the population. In case of absence of participant during the first visit, a second visit will be scheduled. In absence of participant during the second visit, no additional visit will be planned.

In case of positive HCV RDT, 5 blood spots will be collected immediately on DBS, put in a specific plastic bag with the ID number and sent to UHS (Rodolphe Merieux laboratory) for HCV RNA extraction and amplification. Results will be sent back to the referral health center of each village and nurses will be in charge to give result to the participant and to refer to care in case of active infection (systematic appointment + phone call if the participant doesn't come).

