### **Testing phase for Arm 1**

The testing phase for arm 1 will take place in health center. During this visit, the investigator:

- Check to confirm that 1/ the participant is in the list of selected HH (2) the number on the participant's voucher match with the second part.
- Check eligibility criteria
- Collect the written consent form
- Attribute a identification code in the study
- Complete the confidential list including personal information (address, phone number) and keep it in a secured cupboard in the health center
- Fill the screening form
- Perform the HCV RDT on a finger stick capillary whole blood
- Give the result to the participant
- Provide specific counseling to avoid future transmission in case of negative result

- Collect blood sample (5 mL EDTA tube) in case of positive RDT and send it to Provincial hospital laboratory to collect plasma. Plasma will be sent to UHS with the ID number to perform HCV RNA
- Give an appointment to participant to receive the result of HCV RNA

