### **Testing phase for Arm 2**

The testing phase for arm 2 will take place directly in the household of participant or in a specific location in the village. During this visit, the CHW:

- Check eligibility criteria
- Provide oral information, information sheet
- Collect the written consent form and give an ID number
- Complete the confidential list including personal information (address, phone number) and keep it in a secured cupboard
- Fill the screening form
- Perform the HCV RDT on a finger stick capillary whole blood
- Give the result to the participant
- Provide specific counseling to avoid future transmission in case of negative result
- Collect DBS (5 spots) on a finger stick capillary whole blood in case of positive RDT and put it in a specific plastic bag with the ID number
- Keep the DBS in HC in the fridge and send to UHS on a regular basis
- Give an appointment to participant to receive the result of HCV RNA

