#### **Primary outcome**

The percentage, and its 95% confidence interval, of persons tested for HCV RDT AND HCV RNA and aware of their status among the total number of persons eligible residing in the region where the intervention takes place will be compared between the 2 arms.

An analysis stratified on age and province of location will also be performed.

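### Eligibility and the uptake denominators cover all residents of the area, whereas the sampling and sample size cover only selected households, and only arm 1 checks the household list

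*Protocol*

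**What the plan says.** **Who is eligible.** Section 6 of the protocol asks for age over 40, consent, and "Residing in the study area". The Study Summary says the same. Neither requires the person to live in a selected household.

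**Who is offered testing.** Section 5 (Study overview) sets out a multistage sample for each geographic area, hence for both arms: "A Simple random sampling (SRS) method will be realized to select 100 households per village within the 10 selected villages". Its last step offers the study to everyone over 40 in each selected household.

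**What uptake is divided by.** The primary endpoint in section 7 is a count "among the total number of persons eligible residing in the region where the intervention takes place". Antibody uptake and case detection use the same base. Linkage to care is taken "among the estimated total number of persons with active infection residing in the region where the intervention takes place". Section 14 repeats the primary definition: "aware of their status among the total number of persons eligible residing in the region where the intervention takes place". The protocol does not define the region.

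**How selection is enforced.** In section 9, arm 1 staff confirm that "the participant is in the list of selected HH" and match the voucher halves. This step is listed apart from the eligibility check. The corresponding text for the community arm reads: "The testing phase for arm 2 will take place directly in the household of participant or in a specific location in the village". Its steps include an eligibility check but no household list. Section 8 adds that arm 2 visits are arranged through the village head, whose task is to tell the villagers about them. It allows the village location only where there are obstacles to testing at home.

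**The concern.** The protocol describes two populations. The sampling and the sample size concern people over 40 in sampled households. The inclusion criterion and every uptake denominator concern all residents of an area or region. An analyst who follows the endpoint definition as written would divide by many people who were never offered a test, and the result would depend on how large the area is rather than on the testing strategy alone.

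A second gap follows. Because being on the household list is not part of eligibility, it limits enrolment only where a separate step says so, and that step is written for arm 1 only. If the denominator is the sampled households, an unlisted resident tested in arm 2 would add to the numerator and not to the denominator, with no counterpart in arm 1. The primary, antibody-uptake and case-detection comparisons are all exposed to some degree.

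**Working it through.** **Step 1. Reproduce the planned figure.** Inputs: 2 provinces, 4 geographic areas per province, 10 villages per area, 100 households per village (section 5); 4 people per rural household, 25% aged over 40 (section 14), so 4 × 0.25 = 1 person over 40 per household.

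- Households: 2 × 4 × 10 × 100 = 8,000
- People over 40: 8,000 × 1 = 8,000
- Clusters of 50: 8,000 / 50 = 160

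Both totals equal those in section 14 and the Study Summary. The base the plan was built on is therefore the sampled households.

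**Step 2. Apply the denominator as written.** The highest possible uptake is

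cap = people offered testing / people over 40 in the region.

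Since the region is undefined, three readings are shown.

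| Reading of the region | People over 40 | Offered | Cap | 60% / 80% in the sample becomes |
|---|---|---|---|---|
| Three operational districts of 100,000 (sections 3 and 5) | 3 × 100,000 × 0.25 = 75,000 | 8,000 | 10.7% | 6.4% / 8.5% |
| Three operational districts of 200,000 | 3 × 200,000 × 0.25 = 150,000 | 8,000 | 5.3% | 3.2% / 4.3% |
| One average commune per area, 107 communes | 1,000,000 / 107 × 0.25 = 2,336 | 1,000 | 42.8% | 25.7% / 34.2% |
| One average commune per area, 103 communes | 1,000,000 / 103 × 0.25 = 2,427 | 1,000 | 41.2% | 24.7% / 33.0% |
| Selected villages of 150 households (assumed) | 150 per village | 100 | 66.7% | 40% / 53% |
| Selected villages of 400 households (assumed) | 400 per village | 100 | 25% | 15% / 20% |

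The commune rows use about one million inhabitants per province (section 5). They assume that an area is a single commune, which the protocol does not state; with two communes the cap halves to about 21%. Village size is not given either. With H households per village the cap is 100/H, so 80% would be attainable only if H ≤ 100/0.80 = 125, and 60% only if H ≤ 100/0.60 ≈ 167. At H = 150, reaching 60% would need 60/66.7 = 90% uptake within the sample.

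**Step 3. Show the dependence on size.** Suppose uptake within the sample is 70% in both arms, with villages of 200 households in arm 1 and 150 in arm 2 (assumed). The written definition gives 0.70 × 100/200 = 35% and 0.70 × 100/150 = 46.7%. The difference of 11.7 points comes from village size alone.

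**Step 4. Size the effect of unlisted people in arm 2.** Section 14 plans 80 clusters of 50 per intervention, so 80 × 50 = 4,000 people per arm. The allocation text in section 5 does not itself say that the areas are split equally, so this is an assumption. For each 100 unlisted people tested and counted:

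- Antibody uptake: 100 / 4,000 = 2.5 points.
- Primary outcome, if people with a negative rapid test count as complete: also 2.5 points.
- Primary outcome, if an RNA test is required literally: RNA follows only a positive rapid test, expected in 5%, so 100 × 0.05 = 5 people and 5 / 4,000 = 0.125 points.

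**The case against.** The strongest reply is that section 5 governs both arms and section 14 applies uptake to the 8,000, so the intended denominator can be recovered and the regional wording is loose drafting. That is fair as to intent. It still leaves the primary endpoint, its analysis and the inclusion criterion stating a different population, and the intended base prevails only if the reader sets the written definition aside.

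On the list check, the reply is that arm 2 workers go to the household, so they hardly need a voucher match. The village site is an exception, the village head's notice announces visits rather than offering tests to all, and the participant code includes a household code. All of this lowers the likelihood of unlisted testing. None of it makes selection a condition of testing in arm 2, and the protocol does not say that the code must belong to a selected household or that others will be removed.

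A reader might infer that unlisted testing could account for much of the planned 20-point difference in the primary outcome. The documents do not support that. They give neither an attendance rate for non-selected residents nor a village size, and the effect on the primary outcome is small if RNA testing is required. If the base were people with a positive rapid test, as the figure of 300 to be screened for RNA in section 14 might suggest, unlisted people would enter numerator and denominator together and the mechanism would largely disappear.

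**Conclusion.** The contradiction stands. The residence criterion and the uptake denominators do not match the sampling or the sample size, which agree with each other exactly at 8,000 people and 160 clusters. Followed literally, uptake is capped at about 5–11%, 41–43% or 25–67% depending on what the region means. The planned 80% is unreachable on each of these readings and 60% on most. These caps rest on the stated population figures, on one commune per area for the second range, and on assumed villages of 150–400 households for the third. They do not show that the trial cannot reach its targets on the intended base; they show that the written base is the wrong one.

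The missing list check in arm 2 is a possible, not a demonstrated, bias towards the community arm. Its size is 2.5 points of antibody uptake per 100 unlisted people on 4,000 per arm. For the primary outcome it is the same only if people with a negative rapid test count as complete, and about one-twentieth of that otherwise.

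**What to change.** - In section 6 and the Study Summary, replace the residence criterion with residence in a household selected in step 3 of the section 5 sampling.
- In section 7, section 14 and the Study Summary, base all uptake denominators on residents over 40 of those selected households, including the linkage denominator, which should count active infections in the same households.
- In section 9, give arm 2 the selected-household check that arm 1 already has.
- In both arms, record anyone tested who is not on the list, but leave them out of the numerator.
- If testing is already complete, make the check at analysis by matching each household code to the list of selected households, and report how many people are removed in each arm.

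The cost is wording and one check against a list that the section 5 sampling already produces. The downside is that non-selected villagers who present are not counted.
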